### **Visit 1. Randomization**

- PCR
- Review medical history
- Review medication history
- Measure vital signs (body temperature, pulse, blood pressure).
- Blood extraction for immune response evaluation.
- Blood extraction for lab safety determinations.
- Randomization.
- Pregnancy test

### **Vaccination arm**

- Review criteria for cancellation of vaccination.
- Administer the trial vaccine dose according to the subject's assignment and administration guidance.

- Observe the subject on site for at least 15 minutes following vaccination for safety monitoring. At the end of the observation period, record the occurrence of any AEs following trial vaccination.

**Visit 2 (Day 7±2)**

- Inquire about AEs and general well-being of the participant since the administration of vaccine dose. Record any AEs, ‘solicited’ and ‘unsolicited’ AEs, SAEs and MAAE.
- Review medication history
- Measure vital signs (body temperature, pulse, blood pressure).
- Blood extraction for immune response evaluation

**Visit 3 (Day 14±3)**

- Inquire about AEs and general well-being of the participant since the administration of vaccine dose. Record any AEs, ‘unsolicited’ AEs, SAEs and MAAE.
- Review medication history
- Measure vital signs (body temperature, pulse, blood pressure).
- Blood extraction for immune response evaluation

**Visit 4 (Day 28±3)**

- Inquire about AEs and general well-being of the participant since the administration of vaccine dose. Record any AEs, ‘unsolicited’ AEs, SAEs and MAAE.
- Review medication history
- Measure vital signs (body temperature, pulse, blood pressure).
- Blood extraction for immune response evaluation
- Lab determination

**Control arm (Group 2)**

- Review criteria for cancellation of vaccination.
- PCR
- Administer the trial vaccine dose according to the subject’s assignment and administration guidance.
- Observe the subject on site for at least 15 minutes following vaccination for safety monitoring. At the end of the observation period, record the occurrence of any AEs following trial vaccination.

**Visit 5 (Day 90±10 or 56±3):**

- Inquire about AEs and general well-being of the participant since the administration of vaccine dose. Record any AEs, ‘solicited’ and ‘unsolicited’ AEs, SAEs and MAAE.
- Review medication history
- Measure vital signs (body temperature, pulse, blood pressure).
- Blood extraction for immune response evaluation
- Lab determination at 56±3 for group 2 in case of COMIRNATY vaccination

**Visit 6 (Day 180±10):**

- Inquire about AEs and general well-being of the participant since the administration of vaccine dose. Record any AEs, ‘unsolicited’ AEs, SAEs and MAAE.
- Review medication history
- Measure vital signs (body temperature, pulse, blood pressure).
- Blood extraction for immune response evaluation

**Visit 7 (Day 360±10):**

- Inquire about AEs and general well-being of the participant since the administration of vaccine dose. Record any AEs, ‘unsolicited’ AEs, SAEs and MAAE.
- Review medication history
- Measure vital signs (body temperature, pulse, blood pressure).
- Blood extraction for immune response evaluation

**8.1. Immunogenicity Assessments**

Planned time points for all immunogenicity and clinical efficacy assessments are provided in the the Flow-Chart (section 1.2 Flowchart). Details of the efficacy assessments are provided below.

All samples for immunogenicity test will be sent to “Centro Nacional de Microbiología” for centralized analysis. After all planned test in this protocol are finalized, all samples will be stored in the ISCIII during 15 years. Detailed sampling shipping instructions will be sent to participating sites from the laboratory.

**8.1.1. Primary immunogenicity assessment.**

The primary immunogenicity assessment will take place 14 days after the boost dose by serological response to vaccination as measured by immunoassay. All determinations will be performed at central level in “Centro Nacional de Microbiología”.

**8.1.2. Secondary immunogenicity assessments.**

Secondary immunogenicity assessments will include:

- Serological response to vaccination as measured by immunoassay, 28 days after the COMIRNATY dose.
- Serological response to vaccination as measured by immunoassay at 3, 6 and 12months after the COMIRNATY dose.
- Neutralizing antibody titers at 14 and 28 days and 3, 6 and 12 months after the COMIRNATY dose.

Exploratory assessment includes:

- Cellular response to vaccination (inflammatory cytokine production IFN $\gamma$  and IL2 against SARS-CoV-2 spike protein) as measured by ELISA immunoassay, basal, 14 and 28 days after the boost dose.

## 8.2. Efficacy assessments

Occurrence of confirmed COVID-19 is defined as the presence of a documented positive SARS-CoV-2 test performed within a healthcare facility. Classification of severity will be based on the highest degree of severity during the observation period.

In general, adults with SARS-CoV-2 infection can be grouped into the following severity of illness categories. However, the criteria for each category may overlap or vary across clinical guidelines and clinical trials, and a patient's clinical status may change over time.

- Asymptomatic or Presymptomatic Infection: Individuals who test positive for SARS-CoV-2 using a virologic test (i.e., a nucleic acid amplification test or an antigen test) but who have no symptoms that are consistent with COVID-19.
- Mild Illness: Individuals who have any of the various signs and symptoms of COVID-19 (e.g., fever, cough, sore throat, malaise, headache, muscle pain, nausea, vomiting, diarrhea, loss of taste and smell) but who do not have shortness of breath, dyspnea, or abnormal chest imaging.
- Moderate Illness: Individuals who show evidence of lower respiratory disease during clinical assessment or imaging and who have saturation of oxygen (SpO2)  $\geq 94\%$  on room air at sea level.
- Severe Illness: individuals hospitalized needing oxygen by NIV or high flow, re-breather mask.
- Critical Illness: Individuals who have respiratory failure, septic shock, and/or multiple organ dysfunction.

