| 
Primary immunogenicity endpoint:
 
 
Serological response to vaccination (antibodies against SARS-CoV-2 spike protein) as measured by immunoassay, 14 days after vaccine dose (Group 1) or randomization (Group 2) .
 
 
Secondary immunogenicity endpoint:
 
 
Serological response to vaccination (antibodies against SARS-CoV-2 spike protein) as measured by immunoassay, 28 days after vaccine dose (Group 1) or randomization (Group 2) .
 
SARS-CoV-2 neutralization as measured by virus neutralization assay, 14 and 28 days after vaccine dose (Group 1) or randomization(Group 2) .
 
Serological response to vaccination (antibodies against SARS-CoV-2 spike protein) as measured by immunoassay at 3, 6 and 12months after randomization.
 
Neutralizing antibody titers at 3, 6 and 12 months after randomization.
 
 
Secondary efficacy endpoints:
 
 
The number of participants with molecularly confirmed COVID-19.
 
Presence and severity of COVID-19 signs and symptoms as measured by Symptoms of Infection with Coronavirus-19 (SIC).
 
 
Primary safety endpoints:
 
 
Solicited local and systemic adverse events (AEs) for a period of 7 days after vaccination.
 
Unsolicited local and systemic adverse events (AEs) for a period of 28 days after vaccination
 
Serious adverse events (SAEs) throughout the study (from randomization until end of the study).
 
Medically-attended adverse events (MAAEs) from the day of vaccination until 6 months after the last vaccination.
 
Abnormal laboratory parameters at 1 month visit after COMIRNATY vaccination.
 
 |                                                                                                                                         |

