**Group 2 (if crossing over is decided) \***

| Visit number                                                                                |                                               | V1                | V2      | V3      | V4                      | V5      | V6      | V7           |
|---------------------------------------------------------------------------------------------|-----------------------------------------------|-------------------|---------|---------|-------------------------|---------|---------|--------------|
| Procedure                                                                                   | Screening                                     | Randomiz
ation | Visit 2 | Visit 3 | Visit 4 –
Boost dose | Visit 5 | Visit 6 | End of study |
| Day ± window                                                                                | 0 to 7 days
before
boost
vaccination | 0                 | 7±2     | 14 ±3   | 28±3                    | 56±10   | 180±10  | 360±14       |
| Screening for eligibility                                                                   |                                               |                   |         |         |                         |         |         |              |
| Eligibility check                                                                           | X                                             |                   |         |         |                         |         |         |              |
| Informed consent                                                                            | X                                             |                   |         |         |                         |         |         |              |
| PCR                                                                                         |                                               | X                 |         |         | X                       |         |         |              |
| Baseline procedures                                                                         |                                               |                   |         |         |                         |         |         |              |
| Randomization                                                                               |                                               | X                 |         |         |                         |         |         |              |

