| Solicited local and systemic adverse events (AEs) for 7 days after vaccine. Via E-diary     |                                               |                   |         |         | X (7 days)              |         |         |              |
| Unsolicited local and systemic adverse events (AEs) for 28 days after vaccine . Via E-diary |                                               |                   |         |         | X           |         |         |              |
| Unsolicited SAEs                                                                            |                                               | X                 |         |         |                         |         |         |              |
| Medically-attended adverse events (MAAEs)                                                   |                                               | X                 |         |         |                         |         |         |              |
| Immune response evaluation                                                                  |                                               | X                 | X       | X       | X                       | X       | X       | X            |

Note: If subjects in Group 2 are not crossed over, the visits will be the same as the groups 1.

1. Temperature, blood pressure and heart rate

2. Lab determination could be performed either at screening visit or randomization

3. Two days per week

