**Participants with COVID19-like signs and symptoms**

| Procedure                                                                                                | Symptoms | Confirmation | Early Follow up | Late Follow up |
|----------------------------------------------------------------------------------------------------------|----------|--------------|-----------------|----------------|
| Day $\pm$ window                                                                                         | Day 1-2  | Day 2-5      | Day 6 to 28     | Day 29 $\pm$ 7 |
| Site to contact participant if COVID19 signs or symptoms are recorded in the e-Diary                     | X        |              |                 |                |
| Case evaluation                                                                                          | X        |              |                 |                |
| Nasal swab sample                                                                                        |          | X            |                 |                |
| Humoral immunity                                                                                         |          | X            |                 | X              |
| Biomarker RNAseq                                                                                         |          | X            |                 | X              |
| Vital signs, including pulse oximetry                                                                    |          | X            |                 | X              |
| Symptoms of infection, including highest body temperature over the last 24 hours measured by participant |          | X            |                 | X              |

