| To assess the humoral immune response against viral variants of SARS-CoV-2, 14 and 28 days after a dose of COMIRNATY in subjects that received a previous single dose of VAXZEVRIA.                                            | 
-Serological response to vaccination (antibodies against SARS-CoV-2 spike protein) as measured by immunoassay at 3, 6 and 12months after the boost dose.
 
- SARS-CoV-2 neutralization as measured by virus neutralization assay at 3, 6 and 12 months after the boost dose.
                                                                                                                                                                                                                 |
| Secondary efficacy objective                                                                                                                                                                                            |                                                                                                                                                                                                                                                                                                                                                                                                                                                                                                          |
| To assess the occurrence of symptomatic molecularly confirmed COVID-19 and severity of COVID-19 signs and symptoms after the administration of a dose of COMIRNATY in subjects that received a prior single dose of VAXZEVRIA. | 
- The number of participants with molecularly confirmed COVID-19.
 
- Presence and severity of COVID-19 signs and symptoms as measured by Symptoms of Infection with Coronavirus-19 (SIC).
                                                                                                                                                                                                                                                                                                   |

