### **9.3.3. Secondary endpoint(s) analysis**

Secondary immunogenicity endpoints (serological response and neutralizing antibodies at each time point) between the two arms will be tested by one-tailed t-test assuming symmetric distribution of lognormal transformation. Geometric means will be calculated as the mean of the assay results after making the logarithm transformation and then exponentiating the mean to express results on the original scale. One-sided 95% CIs will be obtained by taking natural log transforms of concentrations/titers, calculating the 95% CI with reference to the t-distribution, and then exponentiating the confidence limits. In other case, Mann-Whitney-Wilcoxon test will be used.

For secondary efficacy objectives, the absolute and relative frequencies of individuals with molecularly confirmed COVID-19 and SIC will be compared through the two-tailed chi-square test and alpha error equal to 0.05.

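### COVID-19 cases are defined without symptoms although the objective is symptomatic disease, and if crossover goes ahead only Group 2 has a scheduled PCR after baseline

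*Protocol*

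**What the plan says.** The protocol describes a COVID-19 case in three ways.

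- **Objective** (Section 1.1 and Table 3.1): "To assess the occurrence of symptomatic molecularly confirmed COVID-19 and severity of COVID-19 signs and symptoms", after a COMIRNATY dose.
- **Endpoint** (Section 1.1, and again in Table 3.1 beside that objective): "The number of participants with molecularly confirmed COVID-19". Symptoms are not required. A second endpoint scores signs and symptoms with the SIC instrument but is not joined to the first.
- **Definition** (Section 8.2): "Occurrence of confirmed COVID-19 is defined as the presence of a documented positive SARS-CoV-2 test performed within a healthcare facility". The severity list that follows opens with a category for people who test positive "but who have no symptoms that are consistent with COVID-19".

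The analysis is in Section 9.3.3: "individuals with molecularly confirmed COVID-19 and SIC will be compared through the two-tailed chi-square test", at an alpha of 0.05.

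The testing schedule is in Section 1.2 and the visit lists of Section 8. Both arms have a PCR at Visit 1. Group 1 has no other scheduled PCR, and the general Visit 4 list has none. The Group 2 crossover flowchart marks a second PCR at Visit 4, and the control-arm list under Visit 4 places it before the dose. That flowchart is conditional: "If subjects in Group 2 are not crossed over, the visits will be the same as the groups 1". Other case-finding starts from symptoms and makes no distinction by arm: "Site to contact participant if COVID19 signs or symptoms are recorded in the e-Diary".

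**The concern.** A symptom-free participant with a positive PCR is a case under Section 8.2 and under the endpoint, but not under the objective. The protocol therefore does not settle what the chi-square test compares.

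The mismatch has a direction. If looser counting affected both arms alike, it would mainly blur the endpoint. Here, once controls are crossed over, one arm has a scheduled test of symptom-free people at Day 28 and the other does not. Any asymptomatic infection found at that visit raises the control count, while the same infection in Group 1 would normally go unseen. The arms can then appear to differ through detection alone.

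Because the Visit 4 PCR comes before the control's dose, ending the comparison at the dose would not remove these positives. The cut-off would have to fall before the Visit 4 sample.

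**Working it through.** The protocol states no COVID-19 rate, sample size or power for this endpoint, so there is no figure of its own to reproduce. The check has two parts.

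**1. Does a symptom-free Visit 4 positive count?**

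- Section 6.4 says the study is conducted within hospitals, so a positive trial PCR is a documented positive in a healthcare facility and satisfies Section 8.2.
- It is a molecular test, so it also satisfies the endpoint wording and the wording of Section 9.3.3.
- It does not satisfy the objective, which requires symptoms.
- Nothing in the protocol excludes scheduled PCR results from the count.

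**2. How large could the effect be?**

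Inputs from the protocol: 400 participants in Group 1 and 200 in Group 2 (Section 1.1), and a two-sided chi-square test at 0.05 (Section 9.3.3).

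Assumed inputs: the same true risk s = 1% by Day 28 in both arms; asymptomatic positivity q at Visit 4 of 0.5%, 1% or 2%; every control crossed over and tested; no asymptomatic positives found in Group 1 after baseline.

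Expected cases in Group 1 = 400 × s = 4. Expected cases in Group 2 = 200 × s + 200 × q = 2 + 200q. Apparent risk ratio = s / (s + q).

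The rejection rate comes from exact binomial enumeration of the uncorrected chi-square test. There the control probability is s + (1 − s)q, so that nobody is counted twice; expected control cases become 2.99, 3.98 and 5.96 instead of 3, 4 and 6.

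| q | Group 1 | Group 2 | Apparent risk ratio | Chi-square rejects | Rejects in favour of COMIRNATY |
|---|---|---|---|---|---|
| 0 | 4/400 | 2/200 | 1.00 | 3.97% | 3.27% |
| 0.5% | 4/400 | 3/200 | 0.67 | 9.35% | 9.09% |
| 1% | 4/400 | 4/200 | 0.50 | 18.50% | 18.40% |
| 2% | 4/400 | 6/200 | 0.33 | 43.32% | 43.31% |

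**Sensitivity to the assumed rates**

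- Varying s from 0.5% to 3%, the rejection rate is 3.97% to 4.94% with q = 0, 6.79% to 13.55% with q = 0.5%, 10.61% to 27.02% with q = 1%, and 23.37% to 57.54% with q = 2%.
- Section 9.3.3 sets no Day 28 cut-off, and each participant is followed for 1 year. If a longer window brings s to an assumed 5% or 10% while q stays at 1%, the ratio is 0.05/0.06 = 0.83 or 0.10/0.11 = 0.91.
- If only half the controls are crossed over and tested, q is in effect halved: at s = 1% and q = 1% the ratio is 1/(1 + 0.5) = 0.67 instead of 0.50.

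**The case against.** The strongest reply is that the Visit 4 PCR was never meant to feed the endpoint. In both flowcharts the PCR row sits under eligibility screening, not endpoint assessment. At Visit 4 it stands beside the review of criteria for cancelling vaccination, so it reads as a pre-dose check. Case-finding has its own symptom-triggered table, and the endpoint is paired with a symptomatic objective. Counting rules may also be set out in the SAP, which is not shown. This is fair as to intent, and it makes counting these positives a literal reading of Section 8.2, not a declared plan. It does not remove the contradiction: the protocol itself fixes a definition that admits results its objective excludes.

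A reader might also infer that asymptomatic infections are found and counted in Group 2 alone. The documents do not support that, for three reasons:

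- Both arms have a Visit 1 PCR. Positives there are balanced in expectation by randomisation.
- An incidental positive in any healthcare facility counts in either arm.
- Without crossover, Group 2 follows the Group 1 visits and the asymmetry never arises. Crossover depends on the Day 14 result and on public health recommendations (Section 4.1).

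Nor does the protocol clearly make antigen-only positives endpoint cases. Antigen tests appear only in the general severity grouping of Section 8.2, and the tested endpoint is molecularly confirmed disease.

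Finally, the illustrated ratios rest on assumed rates, and the highest q is twice the assumed 28-day risk. In absolute terms the effect is 1, 2 or 4 control cases on a secondary endpoint. That stands, and it limits the weight of the numbers. The direction does not depend on them.

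**Conclusion.** The point holds in a conditional form. The objective, the endpoint and Section 8.2 disagree on whether symptoms are required, whether or not crossover takes place. If crossover is decided, and if Section 8.2 is applied as written, the Visit 4 PCR creates unequal detection after baseline that favours COMIRNATY.

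The size cannot be known from the protocol. Under equal true risks of 1% by Day 28, full crossover and 0.5% to 2% asymptomatic positivity at Visit 4, the apparent risk ratio runs from 0.67 to 0.33 with no true effect. It moves closer to 1 with a longer window and more cases, or with fewer controls tested. These figures illustrate what the wording permits; they do not predict the trial's result. The endpoint is secondary and the sample size was set for immunogenicity, so the primary analysis is not affected. The correction is still worth making, because crossover is what the protocol plans to consider if its primary hypothesis is confirmed.

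**What to change.** Use one definition in Section 1.1, Table 3.1 and Section 8.2:

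- An endpoint case is symptomatic COVID-19 with onset after randomisation and a positive nucleic acid test.
- Positives from the scheduled Visit 1 and Visit 4 PCRs without symptoms do not count in the Section 9.3.3 test. They are listed separately by arm.
- A participant who is PCR-positive at Visit 4 and then develops compatible symptoms counts as a case, within a period that the sponsor should state.

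The last rule is needed because Section 8.2 recognises presymptomatic infection. If only symptom-triggered samples counted, a control found positive at Visit 4 who became ill afterwards, without a further positive swab, would be lost. That loss would fall on controls only and would reverse the bias.

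The cost is a wording change in three places, carried into the SAP, and slightly fewer counted cases. No visit, sample or procedure changes.
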